#### 2.7.8. Secondary Endpoint Analysis

Analyses of secondary endpoints are exploratory and hypothesis-generating, as the study is not powered for statistical significance in these measures. Findings will guide future studies.

Variability in Platelet Function

Objective: Assess inter-individual variability in platelet inhibition across timepoints.Analysis:
Continuous values (% inhibition) summarized at baseline, discharge, and 6 weeksRepeated measures ANOVA or Friedman test for within-patient changesBoxplots and line graphs used for visualization

Prevalence of Platelet Resistance

Objective: Determine the proportion of patients with inadequate platelet inhibition.Analysis:
Categorical resistance status reported for each timepoint with 95% confidence intervalsChanges in resistance status analyzed using McNemar’s test for paired categorical data

Demographic and Clinical Predictors of Platelet Function

Objective: Explore associations between patient characteristics and platelet responsiveness.Analysis:
Univariable and multivariable linear regression for continuous % inhibition outcomesConsidered variables: age, sex, BMI, renal function, diabetes, and number of graftsSelection guided by clinical relevance and statistical significance (*p* < 0.1)

Impact of Platelet Resistance on Clinical Decision-Making

Objective: Evaluate whether platelet resistance influences treatment decisions, including DAPT use and discharge timing.Analysis:
Comparisons of DAPT prescription rates between resistant and non-resistant patients using chi-square or Fisher’s exact testLogistic regression to explore predictors of treatment decisions if data allows

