This observational study seeks to address the unmet need for robust data linking perioperative platelet function test (PFT) results with clinical outcomes following CABG. The primary objective of this study is to determine the association between perioperative platelet function test results and clinical outcomes, including major adverse cardiovascular and cerebrovascular events (MACCE), postoperative bleeding, and the need for surgical re-exploration. In this study, MACCE is defined as a composite of myocardial infarction, non-fatal stroke, and cardiovascular death, assessed at 30 days and one year following CABG. The secondary objectives include assessing the prevalence of aspirin and clopidogrel resistance in CABG patients using platelet mapping, identifying demographic and clinical predictors of antiplatelet resistance—such as age, sex, diabetes, renal function, ethnicity, BMI, and surgical technique—and evaluating temporal trends in platelet responsiveness from the preoperative baseline through early and late postoperative periods. Additionally, the study will explore the relationship between high platelet reactivity and the need for postoperative escalation of care, including ICU readmission, inotropic support, and transfusions. Lastly, it will assess the feasibility of integrating PFT into the perioperative care pathway to support individualized antiplatelet management in future interventional studies.

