### 2.7. Statistical Analysis

#### 2.7.1. Baseline Characteristics and Study Flow

Baseline characteristics will be assessed to ensure comparability across participant groups. The following variables will be evaluated:Demographics: Age (continuous), sex (categorical), ethnicity (categorical), BMI (continuous)Clinical history: Diabetes status (categorical), renal function (eGFR, continuous), hypertension (categorical), previous PCI or MI (categorical)Operative details: On-pump vs. off-pump surgery (categorical), number of grafts (continuous), use of antiplatelet agents (categorical)

Continuous variables will be reported as means with standard deviations or medians with interquartile ranges, depending on data distribution. Categorical variables will be presented as frequencies and percentages. Group differences will be assessed using appropriate statistical tests:Student’s *t*-test or Mann–Whitney U test for continuous variablesChi-square or Fisher’s exact test for categorical variables

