### 3.3. Secondary Analyses

Secondary analyses will investigate potential predictors of platelet function variability, including demographic and clinical factors such as diabetes status, renal function, smoking history, and surgical approach. Multivariable regression models will be employed to adjust for key covariates and assess independent associations with platelet responsiveness.

Additionally, the feasibility of integrating PFT into routine perioperative workflows will be examined. The study will evaluate whether PFT results influence clinical decision-making, including modifications in antiplatelet therapy or postoperative management.

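### The predictor model selects variables partly at p < 0.1 in the same data, and its candidate list omits surgical technique, ethnicity and antiplatelet use, all of which are collected

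*Protocol article*

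**What the plan says.** Section 2.7.8 of the protocol article sets out univariable and multivariable linear regression for continuous percentage inhibition. The candidates are "variables: age, sex, BMI, renal function, diabetes, and number of" grafts, and selection is to be "guided by clinical relevance and statistical significance", with p < 0.1 as the threshold. How clinical relevance and the p-value combine is not stated.

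Other sections name different predictors. The secondary objective in the Introduction gives factors "such as age, sex, diabetes, renal function, ethnicity, BMI, and surgical technique". Section 2.6.2 repeats that list without ethnicity. The Abstract also names surgical technique. Section 3.3 names "diabetes status, renal function, smoking history, and surgical approach" and promises multivariable models for independent associations.

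The baseline variables in section 2.7.1 include "On-pump vs. off-pump surgery (categorical"), "ethnicity (categorical") and the use of antiplatelet agents. Section 2.1.4 makes clear that clopidogrel is given to some patients only. Section 2.7.8 also states: "Analyses of secondary endpoints are exploratory and hypothesis-generating".

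**The concern.** There are three linked problems.

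- **Selection.** If a variable stays because its p-value is small in the data that also supply its estimate, the reported coefficient is conditional on having come out large. Weak predictors are then overstated and their nominal 95% intervals cover less often than claimed. Section 2.7.9 tells the reader to rely on effect sizes and confidence intervals, which are the quantities affected.
- **Mismatch of lists.** Surgical technique is a named secondary-endpoint predictor, but the only section that specifies the predictor model leaves it out. Ethnicity is in the Introduction's objective and is also left out.
- **Drug exposure.** The ADP channel is read as clopidogrel response. Without a term for the agents taken, that channel mixes users and non-users, and a characteristic that merely tracks prescribing could look like a predictor of responsiveness.

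At stake is whether the reported predictors, which are meant to guide later studies, have the right size and cover the factors the study set out to examine.

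**Working it through.** **Step 1: the predictor lists side by side.**

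| Variable | Abstract | Introduction | 2.6.2 | 2.7.8 model | 3.3 | Listed in 2.7.1 |
|---|---|---|---|---|---|---|
| Age, sex | no | yes | yes | yes | no | yes |
| BMI | yes | yes | yes | yes | no | yes |
| Renal function, diabetes | yes | yes | yes | yes | yes | yes |
| Number of grafts | no | no | no | yes | no | yes |
| Surgical technique | yes | yes | yes | **no** | yes | yes |
| Ethnicity | no | yes | no | **no** | no | yes |
| Smoking | no | no | no | **no** | yes | not by name |
| Antiplatelet agents | no | no | no | **no** | no | yes |

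Number of grafts does not stand in for technique, because section 2.7.1 lists the two separately. Smoking is not in any objective or endpoint. Its mismatch is between sections 2.7.8 and 3.3 only, and the cardiovascular risk factors mentioned in section 3.1 may cover its collection.

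**Step 2: size of the selection effect.** The plan gives no figure to reproduce and no expected slopes, so the slopes here are assumptions. The sample sizes come from section 2.1.1: a target of 100, and about 80 after 20% attrition (100 × 0.8). For each slope, 20,000 data sets were simulated with standard normal predictor and outcome. A univariable regression was fitted and the estimate kept only if p < 0.1, so the p-value acts alone.

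| True slope | N | Chance of selection | Mean selected estimate ÷ truth | Coverage of 95% CI if selected |
|---|---|---|---|---|
| 0.10 | 80 | 23% | 2.36 | 87% |
| 0.15 | 80 | 38% | 1.73 | 93% |
| 0.20 | 80 | 56% | 1.39 | 95% |
| 0.30 | 80 | 86% | 1.09 | 97% |
| 0.10 | 100 | 26% | 2.15 | 89% |
| 0.15 | 100 | 44% | 1.58 | 94% |
| 0.20 | 100 | 64% | 1.29 | 96% |
| 0.30 | 100 | 92% | 1.05 | 97% |

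Inflation is large for weak predictors and small for strong ones. Coverage falls clearly short only at the weakest slope.

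**Step 3: is selection needed?** Counting one parameter per variable:

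- the present six: 80/6 = 13.3 and 100/6 = 16.7 patients per parameter;
- eight, adding technique and antiplatelet agents: 80/8 = 10.0 and 100/8 = 12.5;
- ten, adding ethnicity and smoking as well: 80/10 = 8.0 and 100/10 = 10.0.

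For a linear model with a continuous outcome, the eight-variable version is workable without screening.

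**The case against.** The analysis is declared exploratory, p-values are to be read cautiously, and clinical relevance stands beside the p-value, so the rule is not a pure screen. The plan does not say that the p-value is univariable. The predictor lists elsewhere are introduced as examples, and an article may leave exact covariates to a fuller plan. All of this lowers the severity. It does not remove the point: the article does fix a list and a threshold, the list conflicts with its own endpoint, and caution about p-values does not correct an inflated coefficient.

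Two stronger readings are tempting, and neither is supported.

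- **That the predictor objective cannot be answered.** Five of the six predictors in section 2.6.2 are in the model, technique and ethnicity are among the listed baseline variables, and section 3.3 does intend to examine surgical approach. What is missing is a matching analysis in section 2.7.8.
- **That screening multiplies false positives.** With six independent null candidates, the chance that at least one passes p < 0.1 is 1 − 0.9^6 = 47%, but a fixed six-variable model has essentially the same chance of showing some p < 0.1. Likewise, a null variable that passes has a 0.05/0.10 = 50% chance of its screening p-value being below 0.05, which is true of any p-value. In simulations of six null candidates (6,000 runs per setting), the chance of any p < 0.05 was about 26% with or without the screen when candidates were independent. With correlation 0.3 it was about 18% to 20% screened against 24% to 26% fixed. The harm lies in distorted estimates of retained weak effects.

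It is also fair that few patients may take clopidogrel, so the ADP model may rest on less information than the ratios in the working suggest.

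**Conclusion.** The point holds at minor to moderate severity. As written, section 2.7.8 would overstate weak predictors, by roughly 1.3 to 2.4 times for standardised slopes of 0.10 to 0.20 at 80 to 100 patients and by 1.1 times or less at 0.30. Interval coverage would drop to about 87% to 89% at the weakest slope and be near nominal or better from 0.20 upward. These figures rest on assumed slopes, normal data and the p-value acting alone. If clinical relevance keeps variables in regardless of p, the distortion is smaller, but the plan does not say how the two criteria combine.

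The omission of technique and ethnicity is plain from the text and needs no assumption. The omission of antiplatelet use follows from section 2.1.4 together with how the ADP channel is interpreted. The documents give no figure for how much of the variation in inhibition the drug taken explains, so no size is put on that part.

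**What to change.** In section 2.7.8, delete the p < 0.1 rule. For each channel (AA and ADP), pre-specify one linear model of percentage inhibition with age, sex, BMI, eGFR, diabetes, number of grafts, on-pump or off-pump surgery, and antiplatelet agents taken at sampling. Keep all terms whatever their p-values and report every coefficient with its 95% confidence interval. Name the timepoint modelled, since the operative variables can bear only on the discharge and six-week samples.

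Reconcile the remaining lists: either add ethnicity to the model or remove it from the Introduction's objective, and either add smoking to sections 2.7.8 and 2.7.1 or remove it from section 3.3.

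The cost is wording only. Individual intervals will be slightly wider than after selection, and if ethnicity or regimen has several levels there will be fewer patients per parameter than the ratios shown. Levels should therefore be grouped in advance. No new data are needed, except smoking if it is kept and not already recorded.

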#### 2.7.9. Handling of Multiplicity

No formal adjustments for multiple comparisons will be made, as these analyses are exploratory. All *p*-values will be interpreted cautiously, with emphasis placed on effect size and confidence intervals.

### 2.8. Study Governance and Ethical Considerations

#### 2.8.1. Committees Involved in the Study

This study is a non-randomised, observational, single-centre investigation; therefore, formal oversight by an Independent Data Monitoring Committee (IDMC) or Trial Steering Committee (TSC) is not required due to the minimal risk to participants and the non-interventional nature of the protocol. However, oversight will be provided by a Trial Management Group (TMG) to ensure adherence to Good Clinical Practice (GCP), institutional governance policies, and study protocol requirements.

The Trial Management Group (TMG) will be responsible for:Monitoring participant recruitment and follow-upEnsuring adherence to the approved study protocolOverseeing data quality, safety reporting, and compliance with regulatory requirementsAddressing operational issues or protocol deviations

The TMG membership will include:Chief Investigator (CI)Study StatisticianStudy Research NurseData Manager or delegated research coordinatorSponsor representative (if applicable)

The TMG will meet regularly throughout the study and maintain formal records of all discussions and decisions.

#### 2.8.2. Monitoring and Auditing

The necessity for study monitoring or auditing will be determined through an internal Research Office risk assessment, following Standard Operating Procedures (SOPs). Monitoring arrangements will be proportionate to the study’s design, complexity, and risk level. If monitoring or auditing is required, visits will be arranged in advance and conducted in accordance with institutional standards, GCP guidelines, and Sponsor policies.

#### 2.8.3. Direct Access to Source Data

Study-related monitoring, audits, Research Ethics Committee (REC) review, and regulatory inspections will be permitted, ensuring direct access to source data as required. Participants will be informed of these procedures during informed consent, allowing authorised representatives (e.g., Sponsor, REC, Health Research Authority (HRA)) access to relevant sections of their medical records, in strict compliance with data protection and confidentiality regulations.

#### 2.8.4. Ethics and Regulatory Requirements

Before patient enrolment, full regulatory approval for the study will be obtained, including:HRA approval, incorporating REC approvalApproval of study documents (protocol, Participant Information Sheet (PIS), Informed Consent Form (ICF), GP letter)

Recruitment will not commence until formal confirmation of capacity and capability is received from participating institutions, as outlined in HRA approval letters.

Should any substantial amendments to the protocol or study documents be necessary, they will be submitted for HRA and REC approval prior to implementation. Principal Investigators will ensure local compliance with all approvals.

In the event of premature study termination, the CI will notify both the Sponsor and REC within 15 days. A formal study closure notification will be submitted within 90 days of study completion. Additionally, a final study report summarising:Whether study objectives were achievedMain findingsPlans for publication and dissemination

Feedback provided to study participants will be submitted to both the REC and Sponsor within 12 months of study completion.

#### 2.8.6. Insurance and Indemnity

NHS institutions are liable for clinical negligence and other harms to patients under their duty of care. Additionally, NHS institutions employing researchers are responsible for negligent harm resulting from study design.

#### 2.8.7. Publication Policy

Data ownership will reside with the institution sponsoring the study, and study findings will be disseminated through peer-reviewed publications and conference presentations.

#### 2.8.8. Statement of Compliance

This study will be conducted in full compliance with:The protocol approved by the Sponsor and HRASponsor Standard Operating Procedures (SOPs)Good Clinical Practice (GCP)Relevant UK regulations, including the Human Rights Act 1998, the Data Protection Act 2018, and ethical frameworks such as the Declaration of Helsinki (2008 version)

Should any protocol deviations be required to eliminate an immediate hazard to a research subject, they will be reported to the Sponsor and REC as soon as possible.

## 3. Results

### 3.1. Participant Characteristics

Baseline demographic and clinical characteristics will be collected from enrolled participants to assess comparability between groups. Variables evaluated will include age, sex, ethnicity, body mass index, cardiovascular risk factors, preoperative medication use, and surgical approach.

### 3.2. Platelet Function and Clinical Outcomes

Platelet function test results will be analyzed at three timepoints: preoperative baseline, postoperative discharge, and six-week follow-up. The degree of platelet inhibition will be reported as percentage inhibition in response to arachidonic acid and adenosine diphosphate pathways, reflecting aspirin and clopidogrel effectiveness, respectively.

The prevalence of aspirin and clopidogrel resistance in the study population will be determined based on predefined cutoff values from the TEG6s Platelet Mapping system. Differences in platelet responsiveness between groups will be evaluated using repeated measures analysis of variance or non-parametric alternatives, depending on data distribution.

The primary analysis will assess correlations between platelet function test results and major adverse cardiovascular and cerebrovascular events, including myocardial infarction, stroke, cardiovascular death, postoperative bleeding complications, and the need for surgical re-exploration. Univariate correlations will be explored using Pearson or Spearman correlation coefficients, while logistic regression models will estimate the odds ratios for adverse outcomes associated with platelet resistance.

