#### 2.1.4. Standard Medications Permitted

Patients undergoing elective and urgent CABG are expected to receive the following standard antiplatelet regimens:Aspirin (typically 300 mg within 6 h of return from operating theatre followed by 75 mg once daily)Clopidogrel (typically 75 mg once daily, when prescribed)

Additionally, concomitant medications—including beta-blockers, ACE inhibitors, statins, or anticoagulants (such as warfarin or direct oral anticoagulants, DOACs)—may be prescribed as per clinical indications. These will be recorded and accounted for in the final analysis as potential confounding variables affecting platelet function and surgical outcomes.

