### 2.4. Eligibility Criteria

#### 2.4.1. Inclusion Criteria

Adults aged 18 years or olderScheduled for elective or urgent, isolated coronary artery bypass grafting at the study centreExpected to receive standard antiplatelet therapy (aspirin or dual antiplatelet therapy) postoperatively as part of routine careAble and willing to provide written informed consent to participate in the studyWilling to undergo perioperative blood sampling for PFT as per the study protocolAble to understand and comply with study procedures and follow-up requirements

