#### 2.7.4. Primary Endpoint Analysis

The primary objective of this study is to evaluate the association between platelet function test results and clinical outcomes in patients undergoing elective and urgent CABG.

Summary Measures

Platelet function results will be summarized as mean ± standard deviation or median with interquartile range (IQR), depending on data distribution, for:AA channel (aspirin response)ADP channel (clopidogrel response)

Clinical outcomes, including MACCE, bleeding, re-exploration, and transfusion, will be reported as frequencies and proportions.

Method of Analysis

Correlation analysis: Pearson’s correlation for normally distributed data, Spearman’s rank correlation for non-parametric dataLogistic regressionEstimates the odds of postoperative events based on platelet resistance status (resistant vs. non-resistant)Adjusts for potential confounders (age, diabetes, renal function, surgical factors)Hierarchical data structure: Generalized estimating equations (GEE) or mixed-effects models will be used to account for repeated measures of platelet function over time.

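### Resistance is classified by cutoff in the study population rather than in patients taking the drug, so as written it mixes non-prescription with non-response

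*Protocol article*

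**What the plan says.** All of this is in the protocol article.

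- **Who is enrolled.** Under 2.4.1, patients must be expected "to receive standard antiplatelet therapy (aspirin or dual antiplatelet therapy) postoperatively". Aspirin alone is enough, and the criterion concerns postoperative therapy only. Section 2.1.4 lists clopidogrel as "typically 75 mg once daily, when prescribed".
- **When they are tested.** Section 2.5.1 sets three tests: the morning before surgery, discharge, and six weeks.
- **How resistance is assigned.** Section 3.2 states: "The prevalence of aspirin and clopidogrel resistance in the study population will be determined based on predefined cutoff values", with the cutoffs taken from the TEG6s system; 2.6.2 names the same population. Section 3.2 also reads AA and ADP inhibition as the effectiveness of aspirin and clopidogrel respectively. Section 2.7.8 gives the aim as "Objective: Determine the proportion of patients with inadequate platelet inhibition", with status reported at each timepoint and changes tested by McNemar's test.
- **Where the status is used.** The logistic model in 2.7.4 takes resistant versus non-resistant as its exposure and adjusts for "potential confounders (age, diabetes, renal function, surgical factors". Section 2.7.8 also plans "Comparisons of DAPT prescription rates between resistant and non-resistant patients". Its predictor model for percentage inhibition considers age, sex, BMI, renal function, diabetes and number of grafts.
- **What is said about other drugs.** After naming concomitant drugs, including anticoagulants, 2.1.4 says: "These will be recorded and accounted for in the final analysis as potential confounding variables". Antiplatelet use is recorded as a baseline variable (2.7.1), as is preoperative medication (3.1).

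**The concern.** The Introduction treats resistance as variability in patients' response to the agents. A patient who has not been given an agent has no response to it. If the cutoff is applied to everyone, low ADP inhibition carries two meanings: the drug did not work, or it was not given.

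- **Prevalence.** The figure would depend on local prescribing as well as on response.
- **McNemar tests.** A patient off clopidogrel at baseline who starts it after surgery could appear to move from resistant to non-resistant, although only the prescription changed.
- **Logistic model.** The exposure would partly encode who was given DAPT, and regimen is not among the listed confounders. Bleeding is one of the outcomes, so patients labelled resistant might seem protected from bleeding simply because they were on one agent rather than two.
- **DAPT comparison.** Where status comes from the ADP channel, DAPT itself drives the status, which reverses the direction the analysis is meant to examine.
- **Predictor model.** It omits regimen, the most direct determinant of percentage inhibition.

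**Working it through.** The article projects no prevalence and gives no cutoff value, so there is no planned figure to reproduce. The check asks what the stated denominator would produce.

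**Inputs**

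- r = resistance among patients on clopidogrel. Taken as 0.40, the upper figure cited in the Introduction for CABG recipients.
- s = share of patients on clopidogrel at sampling. Not given; varied from 0.3 to 0.9.
- q = chance that a patient not on clopidogrel reads below the ADP cutoff. Not given; 0.7 and 1.0 are shown.
- Being on clopidogrel is equated with being on DAPT, and prescribing is assumed not to depend on resistance.

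**Formulas**

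- Apparent prevalence A = s·r + (1 − s)·q
- DAPT share among those labelled resistant = s·r / A
- DAPT share among those labelled non-resistant = s·(1 − r) / (1 − A)

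**Worked case, s = 0.5**

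- q = 0.7: A = 0.20 + 0.35 = 0.55. DAPT shares are 0.20/0.55 = 36% and 0.30/0.45 = 67%.
- q = 1.0: A = 0.20 + 0.50 = 0.70. DAPT shares are 0.20/0.70 = 29% and 0.30/0.30 = 100%.

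**Range**

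| s | q | Apparent prevalence | DAPT among resistant | DAPT among non-resistant | Untreated share of resistant |
|---|---|---|---|---|---|
| 0.3 | 0.7 | 61% | 20% | 46% | 80% |
| 0.3 | 1.0 | 82% | 15% | 100% | 85% |
| 0.5 | 0.7 | 55% | 36% | 67% | 64% |
| 0.5 | 1.0 | 70% | 29% | 100% | 71% |
| 0.9 | 0.7 | 43% | 84% | 95% | 16% |
| 0.9 | 1.0 | 46% | 78% | 100% | 22% |

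The excess over r is A − r = (1 − s)(q − r). It is zero only if every patient is on clopidogrel (s = 1) or if untreated patients fall below the cutoff exactly as often as treated ones (q = r). Because 40% is an upper figure, r may be lower, and the excess would then be larger. At s = 0.5 and r = 0.2 it would be 0.5 × 0.5 = 25 points (q = 0.7) to 0.5 × 0.8 = 40 points (q = 1).

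**After the fix.** With clopidogrel-treated patients as the denominator, the estimate returns to r whatever s is. The 95% half-width is 1.96·√(0.4 × 0.6/n): about 10 points at n = 100, 14 at n = 50 and 18 at n = 30.

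**The case against.** The strongest reply is that nothing in the article says untreated patients will be called resistant. Its own concept presupposes treatment: the Introduction speaks of response to the agents, and 2.5.1 describes an assay of inhibition in response to therapy. Study population is an ordinary phrase in a condensed article, and a fuller document may restrict the denominator. That may well be the intention. But the article does state a denominator, in 2.6.2 and 3.2, and applies it at a preoperative test for which no drug exposure is required. Taken at its word, the text gives the wrong classification.

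Other parts of the reply stand and limit the point:

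- **The DAPT comparison is not necessarily circular.** Section 2.7.8 names neither channel nor timepoint. AA-channel status measured before the DAPT decision would be a sound comparison, and the text permits it. The artefact arises only with ADP status.
- **The primary analysis as a whole is not invalid.** A reader might infer that it is. But 2.7.4 and 3.2 also correlate platelet function results with outcomes, and the continuous measure is valid for platelet reactivity whatever its cause. For pure prognosis, low inhibition may matter even when it reflects no prescription. Restricting to treated patients or adjusting for regimen then answers a different question, which should be chosen openly.
- **Aspirin is little affected after surgery,** since all patients are expected to receive aspirin or DAPT by then.
- **Section 2.1.4 does not promise adjustment for aspirin versus DAPT.** A reader might take it that way, but the commitment follows a list of concomitant drugs such as anticoagulants. The case for adding regimen rests on its own merits.
- **The secondary analyses are declared exploratory** (2.7.8), and p-values are to be read cautiously (2.7.9).

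**Conclusion.** The point holds as a defect of the text. The stated denominator, the eligibility rule and the reading of ADP inhibition as clopidogrel effectiveness together count non-prescription as non-response. It affects the prevalence endpoint, the McNemar tests, the binary logistic exposure, and the DAPT comparison where status uses the ADP channel. The listed covariates in 2.7.4 and 2.7.8 also omit antiplatelet regimen.

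The size is illustrative. With r = 0.40 and s = 0.5, apparent clopidogrel resistance is 55% to 70%, with a spurious DAPT split of 36% vs 67% to 29% vs 100%, for q between 0.7 and 1. A reader might go straight to the upper end by assuming that every untreated patient reads below the cutoff. The article shows no cutoff value and gives neither s nor q, so it does not support that as a fact. With nearly all patients on clopidogrel, the distortion would be small.

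This should be fixed. It does not rank higher because the continuous primary correlation survives, several of the affected analyses are exploratory, and the drug data needed are already being recorded.

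**What to change.** - In 2.7.8 and 3.2, report aspirin resistance (AA channel) among samples taken on aspirin and clopidogrel resistance (ADP channel) among samples taken on clopidogrel, giving those denominators at each timepoint. Make the endpoint wording in 2.6.2 agree.
- Describe low inhibition in untreated patients as platelet reactivity, separately from resistance.
- Limit each McNemar test to patients on the drug at both timepoints compared.
- Limit the DAPT comparison to AA-channel status measured before the prescribing decision, or drop it.
- Use ADP resistance as a binary exposure in 2.7.4 only within clopidogrel-treated patients. Keep the continuous correlation in all patients, labelled as platelet reactivity.
- Add antiplatelet regimen at sampling to the models in 2.7.4 and 2.7.8, together with anticoagulant use, which 2.1.4 already undertakes to account for.

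The cost is analysis wording plus a check that antiplatelet use is recorded at each test, since 2.7.1 and 3.1 list it only among baseline variables. The statistical price is smaller denominators for clopidogrel resistance: at 40% prevalence, about ±14 points with 50 treated patients against ±10 with 100. Regimen also takes a further parameter in the logistic model.
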